#### Secondary hypotheses

That implementation of the DIVA identification and escalation pathways:

H_2_ Will significantly increase the incidence of first attempt PIVC insertion success for **all patients**.

H_3_ Increases the proportion of patients with DIVA who have ultrasound used at first, or any attempt.

H_4_ Reduces the number of PIVC insertion attempts.

H_5_ Results in higher rates of successful PIVC placement and shorter time-to-therapy.

H_6_ Results in higher rates of alternate device or route use.

H_7_ Reduces post-insertion PIVC failure and complications.

H_8_ Results in increased PIVC dwell time.

H_9_ Is sustainable (i.e. There is no significant reduction in first time insertion success at 3 or 6 months compared to full implementation (month 10).

H_10_ Reduces rates of unnecessary PIVCs.

H^11^ Is cost-effective in Queensland healthcare settings.

H^12^ Reduces rates of cluster level routinely collected rates of primary BSI and S. Aureus BSI.

H^13^ Improves patient/carer and staff satisfaction with insertion procedure.

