### Setting and sampling

DART^3^ is a multi-site study involving three large tertiary hospitals in South-East Queensland, Australia. All hospitals (two adult and one paediatric) are government-funded, university affiliated teaching facilities.

Each hospital has four participating clusters (wards or departments), for a total of 12 clusters. Each cluster begins with a baseline phase, followed by a step up to the implementation phase, where the intervention is introduced, the study is completed by a sustainability phase, divided into three- and six-month time points. The total study timeframe will be 16-months and consist of seven steps. Hospital and cluster characteristics are outlined in Supplementary material 1. Eligible clusters include emergency departments, inpatient wards or critical care units (CCU, ICU) where greater than 10 PIVCs per week are typically inserted. Operating services, which theatres, radiology, rehabilitation, or psychiatric units, were not eligible for inclusion. All hospitalised patients (DIVA or non-DIVA) of any age prescribed a PIVC insertion (standard or long length PIVC) may be included. Patients requiring time-critical intravenous access (e.g., Medical Emergency calls, intraosseous access) will not be included in the study.

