### Sample size

Approximately 40% of studied patients are expected to be DIVA patients (8 per cluster step), and 60% non-DIVA (12 per cluster step). For DIVA patients, we assume baseline first attempt insertion success of 50% (based on meta-analysis [12] and our unpublished data on file) and anticipate a 50% relative improvement to 75% first insertion success [12]. We assume baseline first insertion success in non-DIVA patients of 70%, rising to 80% post- intervention. This is equivalent to an overall change for all patients from 62 to 78% first attempt insertion success. With 240 patients at each of the five data collection periods (baseline plus four steps), there will be > 90% power to detect a significant difference between the usual care and implementation phases (alpha = 0.05). See Supplementary Material 3: statistical analysis plan.

To measure sustainability of the effect of the implementation on the primary endpoint, we will additionally assess 240 patients at each sustainability time point (3 and 6 months). This leads to a total sample size of 1680 observations, consisting of 240 observations at each of the 7 periods (baseline, steps 1–4, 3- and 6-month follow-up).

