***Primary***		
First attempt insertion success in patients identified as DIVA	One needle puncture, by one inserter, to achieve successful insertion of a functional (can be aspirated/flushed) PIVC ^2^	Hospital-based assessments

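### H9 treats a non-significant fall in first-attempt success as proof that the effect was sustained, although with about 96 DIVA patients per time point a substantial partial loss would often pass

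*Protocol article*

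**What the plan says.** H9, in the protocol article under Secondary hypotheses, says the programme is sustainable and then explains, with an i.e., what that means: "There is no significant reduction in first time insertion success at 3 or 6 months compared to full implementation (month 10"). A non-significant comparison is therefore the stated success criterion. The article attaches no margin, confidence limit or power to it.

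The Sample size section describes the data for this question. The purpose is "To measure sustainability of the effect of the implementation on the primary endpoint", and for it "we will additionally assess 240 patients at each sustainability time point (3 and 6 months"). Table 1 gives the primary outcome as "First attempt insertion success in patients identified as DIVA". H9 itself and the maintenance row of Table 1 speak only of first-time insertion success and do not name the DIVA population. The link to DIVA comes through the Sample size section.

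The only power statement in the article, above 90%, is for usual care against implementation.

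**The concern.** Failing to find a significant fall does not show that there was none. Under H9 the verdict becomes easier to reach as the sample gets smaller or noisier, so under-recruitment in the follow-up periods would favour the hypothesis. The comparison uses single periods (month 10 against 3 months, month 10 against 6 months), each with far fewer patients than the main contrast. A fall that removes a large part of the benefit could therefore be reported as sustained. First-time insertion success at 3 and 6 months is the effectiveness measure in the RE-AIM maintenance domain, and 480 of the 1680 planned observations (2 × 240) are collected for it.

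**Working it through.** **Inputs, all from the protocol article**
- Clusters: "Each hospital has four participating clusters (wards or departments), for a total of 12 clusters" (Setting and sampling).
- DIVA share: "Approximately 40% of studied patients are expected to be DIVA patients (8 per cluster step") (Sample size). Hence 12 × 8 = 96 DIVA patients per period, which equals 40% of 240. The article does not print the 96.
- DIVA success: "we assume baseline first attempt insertion success of 50"%, and the authors "anticipate a 50% relative improvement to 75% first insertion success" (Sample size). The planned gain is 25 points.
- Alpha is 0.05. Sidedness is not stated, so two-sided is assumed and one-sided is shown as a sensitivity.
- The intracluster correlation (ICC) is not given. The main H9 figures ignore clustering, and a range is shown below.

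**The plan's own figures reproduce**
- 240 × 7 = 1680 observations.
- All-patient rates: 0.4 × 50 + 0.6 × 70 = 62%, and 0.4 × 75 + 0.6 × 80 = 78%.
- Stepped-wedge power for DIVA patients (Hussey–Hughes variance, 12 clusters, 5 periods, 3 clusters crossing per step): 98.5% at ICC 0, 94.2% at 0.05 and 91.0% at 0.2. The claim of more than 90% holds over that assumed range.

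**Chance that H9 passes when benefit has been lost**

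For a true fall d from p₁ = 0.75 to p₂ = 0.75 − d, with n = 96 per time point and p̄ the mean of the two rates:

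power = Φ{ [d√n − 1.96√(2p̄(1 − p̄))] / √(p₁(1 − p₁) + p₂(1 − p₂)) }

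For d = 0.10: [0.980 − 1.270] / 0.644 = −0.45, so power is 0.326 and the chance of no significant fall is 0.67. For d = 0.125: [1.225 − 1.285] / 0.650 = −0.09, so power is 0.463 and the chance is 0.54 (0.53 by simulation).

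The probability of passing at both follow-ups needs the shared month-10 reference. It was obtained from 400,000 simulated binomial triples with the same fall at each follow-up:

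| True DIVA success at follow-up | Share of 25-point gain lost | Passes at one time point | Passes at both |
|---|---|---|---|
| 70% | 20% | 0.88 | 0.81 |
| 65% | 40% | 0.67 | 0.52 |
| 62.5% | 50% | 0.53 | 0.36 |
| 60% | 60% | 0.39 | 0.23 |
| 50% | 100% | 0.05 | 0.01 |

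A fall must reach about 19 points, roughly three quarters of the gain, before one comparison has 80% power.

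**Sensitivities**
- One-sided 0.05, one time point: 0.55 for a 10-point fall and 0.41 for 12.5 points.
- All patients (240 v 240 from 78%): losing 8 of the 16 points passes 0.48 at one time point and 0.32 at both. Full loss passes 0.03 at one.
- Design effect 1 + 7 × ICC: power for a 12.5-point fall drops from 46% to 42% at ICC 0.02 and 30% at 0.10. This is on the conservative side because the same clusters are compared, although cluster-by-period variation would act the other way.
- Sample size, half the gain lost, one time point: the pass rate is 0.73 with 50 patients per time point, 0.53 with 96 and 0.23 with 200.

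**What a margin-based rule could deliver**

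If success is 75% at both times, SE = √(2 × 0.75 × 0.25 / 96) = 0.0625, and the 95% interval is ±1.96 × 6.25 = ±12.25 points. Power against a margin M is Φ(M / 0.0625 − 1.96). For M = 0.125 this is Φ(0.04) = 0.52, and for M = 0.10 it is 0.36. Reaching 80% at M = 0.125 would take 189 DIVA patients per time point.

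**The case against.** The best case for the plan has several parts.

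- **H9 is secondary.** It does not touch the primary hypothesis, its model or its power. This stands and limits the weight of the point.
- **The natural reading of 3 or 6 months is stricter.** H9 most plausibly requires no significant fall at either time, so the both-time-points column is the relevant one. This also stands. Those probabilities are lower, but 0.52 and 0.36 are still too high for losses of 40% and 50%.
- **The population may be all patients.** H9 does not name DIVA. The larger sample helps, but losing half of the smaller gain still passes both tests about a third of the time.
- **The analysis plan in Supplementary material 3 is not shown and may set a margin.** It may. The objection here is to the rule that the article states, not to a missing margin. A margin in the analysis plan would differ from H9 as worded, so H9 would still need rewording.

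Two stronger readings are tempting and are not supported. A reader might infer that the rule would certify a programme whose benefit had vanished. It seldom would: complete loss passes about 5% of the time at one time point and 1% at both. A reader might also infer that H9 decides scale-up. The article assigns that role to the process evaluation, and three of the four maintenance rows in Table 1 do not depend on this test.

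**Conclusion.** The point holds as a flaw in how a secondary hypothesis is stated. H9 equates non-significance with sustainability, and at the planned size that rule passes both follow-ups with probability 0.52 when 40% of the planned gain is lost and 0.36 when half is lost (0.67 and 0.53 at one time point). It does not hide total loss.

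The figures rest on 96 DIVA patients per time point, a month-10 rate of 75% as planned, the same true fall at both follow-ups, a two-sided 0.05 test and no clustering. The all-patient reading and the one-sided test change the size but do not repair the rule. Nothing here bears on the validity or power of the primary analysis.

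**What to change.** Restate H9 in one of two ways.

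1. Conclude sustained only if the lower 95% confidence limit for the difference (follow-up minus month 10) lies above a margin that the sponsor fixes in advance. Estimate the difference from the clustered model, separately at 3 and at 6 months, with month 10 kept as the reference. State the population, and whether both time points must meet the criterion.
2. Report each change from month 10 with its 95% interval and give no verdict on sustainability.

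Pooling all post-crossover data as the reference to gain precision is not advisable. That pool has 30 cluster-periods × 8 = 240 DIVA patients, of whom only 96 are from month 10. If, as an assumed example, the 144 earlier patients had 65% success and the 96 at month 10 had 75%, the pooled reference would be (144 × 65 + 96 × 75) / 240 = 69%, and a true 6-point decline would appear as none. Pooling 3 with 6 months could likewise mask late decay.

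The cost is a rewording of H9 and matching text in the analysis plan, with no extra patients. The drawback is that the claim becomes harder to make. With an illustrative 12.5-point margin, power is only about 52% per time point if nothing is lost, and lower if both must pass. H9 would then serve mainly as an estimate with its interval.

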### Study design

A stepped wedge cluster randomised trial (SW-CRT) will be used to evaluate the implementation and effectiveness of co-designed DIVA identification and escalation pathways (Fig. 1). The theoretical model for DART3 is outlined in Fig. 2. The RE-AIM (Reach, Effectiveness, Adoption, Implementation, and Maintenance) framework [25, 26] will be used to evaluate the strategy, in which three domains of outcomes will be included: effectiveness outcomes, cost-effectiveness outcomes and implementation outcomes. Effectiveness will be measured using health service and patient outcomes. Implementation evaluation will explore reach, adoption, implementation, and maintenance. The Consolidated Framework for Implementation Research [27] will be used to identify the barriers and facilitators influencing the implementation strategy and to establish the feasibility, acceptability, and sustainability of our DIVA initiatives. The study will be reported in line with Standard Protocol Items: Recommendations for Interventional Trails (SPIRIT) [28]. The completed SPIRIT checklist is provided in supplementary material 7.

**Fig. 1 Fig1:**
[figure not shown]
Study flow diagram

**Fig. 2 Fig2:**
[figure not shown]
Theoretical model for DART^3^ study *Examples of clinical effectiveness outcomes, not all outcomes included

### Setting and sampling

DART^3^ is a multi-site study involving three large tertiary hospitals in South-East Queensland, Australia. All hospitals (two adult and one paediatric) are government-funded, university affiliated teaching facilities.

Each hospital has four participating clusters (wards or departments), for a total of 12 clusters. Each cluster begins with a baseline phase, followed by a step up to the implementation phase, where the intervention is introduced, the study is completed by a sustainability phase, divided into three- and six-month time points. The total study timeframe will be 16-months and consist of seven steps. Hospital and cluster characteristics are outlined in Supplementary material 1. Eligible clusters include emergency departments, inpatient wards or critical care units (CCU, ICU) where greater than 10 PIVCs per week are typically inserted. Operating services, which theatres, radiology, rehabilitation, or psychiatric units, were not eligible for inclusion. All hospitalised patients (DIVA or non-DIVA) of any age prescribed a PIVC insertion (standard or long length PIVC) may be included. Patients requiring time-critical intravenous access (e.g., Medical Emergency calls, intraosseous access) will not be included in the study.

### Intervention description

During the implementation phase, clusters not stepping up and non-participating wards will continue with usual care for PIVC insertion. The DART^3^ intervention involves a co-designed DIVA identification tool (clinical decision-making tool which stratifies the patients’ risk of having DIVA) and escalation pathway tailored to the local health service [1]. All concomitant cares will continue while the patient is enrolled in the trial. PIVC maintenance and removal procedures will be as per local hospital policies and driven by treating clinicians. Once the study PIVC is removed, as decided by the treating clinical team, outcome and adverse event data will be collected for a further 48-hours by clinical research nurses.

### Randomisation and blinding

The intervention will be applied at the cluster (ward) level. Intervention clusters will carry out the DIVA interventions, and clusters that have not been enrolled in the intervention will continue with usual care. Usual care will vary by site and cluster, (predominantly landmark insertion, with ad hoc DIVA assessment and/or escalation to a small number of ultrasound skilled practitioners, typically after multiple failed landmark attempts).

Randomisation to the sequence of implementation occurs at site level and is stratified by hospital, with each cluster a unit of randomisation. Cluster sequence generation is conducted by a centralised, web-based randomisation service (https://randomisation.griffith.edu.au/) to ensure concealment.

All clusters commence in the baseline phase and then in randomly allocated order, one cluster per site steps up to implementation of the intervention, approximately every two months as feasible for the site (stepped-wedge cluster-randomisation schema outlined in Supplementary material 2). Cluster allocations will be revealed to the project manager who will advise the sites on commencement of the baseline phase. This is necessary to allow time to plan cluster implementation strategies. Blinding of patients, clinicians and research staff is not possible due to the nature of the intervention. Outcome assessors apportioning infection outcomes (infectious diseases physician) will be blinded to study phase (baseline or implementation).

### Sample size

Approximately 40% of studied patients are expected to be DIVA patients (8 per cluster step), and 60% non-DIVA (12 per cluster step). For DIVA patients, we assume baseline first attempt insertion success of 50% (based on meta-analysis [12] and our unpublished data on file) and anticipate a 50% relative improvement to 75% first insertion success [12]. We assume baseline first insertion success in non-DIVA patients of 70%, rising to 80% post- intervention. This is equivalent to an overall change for all patients from 62 to 78% first attempt insertion success. With 240 patients at each of the five data collection periods (baseline plus four steps), there will be > 90% power to detect a significant difference between the usual care and implementation phases (alpha = 0.05). See Supplementary Material 3: statistical analysis plan.

To measure sustainability of the effect of the implementation on the primary endpoint, we will additionally assess 240 patients at each sustainability time point (3 and 6 months). This leads to a total sample size of 1680 observations, consisting of 240 observations at each of the 7 periods (baseline, steps 1–4, 3- and 6-month follow-up).

### Implementation approaches

#### Site-specific advisory groups and co-design of DIVA tools and implementation strategies

Advisory groups have and will be established at each hospital comprising of cluster and hospital level clinicians, vascular access experts, nurses and medical managers and educators, quality and safety experts, consumers, and hospital executives. To guide the co-design process, core concepts (e.g., patient risk factors) will be provided by the investigator team as important foundational principles of the tools [1, 17, 24]. These are based on a series of published preliminary work by the investigating team including evidence syntheses [9, 29, 30] and interviews (face-to-face and by telephone) [16, 17] conducted with key stakeholders across hospital and health services. Workshops and teleconference meetings with hospital groups and executives will be used to co-design tools tailored to the local context.

Site-specific advisory groups will also tailor multi-modal implementation strategies that are feasible for hospitals to support capability, opportunity, and motivation to use the DIVA tool and escalation pathway. Implementation strategies (outlined in supplementary material 4) will be underpinned by Michie et al. Behaviour Change Wheel implementation theory [31] with discussions informed by an implementation scientist (LH).

Site advisory group meetings, comprising stakeholders and champions, will continue throughout the study to tailor implementation strategies to ensure they are locally effective. Research nurses (majority skilled ultrasound PIVC inserters), supported by an overall study manager and research assistant will work with investigators, local educators, and clinical managers to deliver the implementation strategies. By the end of implementation, PIVC inserters will be the local accredited workforce, however research nurses will initially undertake bedside teaching and coaching as local inserters learn the ultrasound technique.

#### Pilot of co-designed tools

The draft DIVA identification pathway tool will be pilot tested at the partner hospitals to assess validity and reliability, and to refine for clarity and utility. Face and content validity of the DIVA identification pathway will be assessed using an electronic questionnaire sent via email to the advisory group. Item validity will be determined using a content validity index (CVI). A panel of experts (n ≥ 5 at each site) comprising multidisciplinary vascular access specialists will be asked to provide feedback on the appropriateness and relevance of tool domains/items using a four-point level of agreement (1, not; 2, somewhat; 3, quite; 4, highly) and face validity of the tool. These clinicians will be sourced from the clinical departments of partner hospitals, separate from the advisory group. Item level CVIs will be calculated as the number of experts giving a score of 3 or 4 (item cut off score of 0.75). Face validity tests the appearance of the DIVA identification tool is adequate for its intended purpose. Reproducibility of the DIVA identification tool will be assessed using inter-rater agreement by two PIVC inserters in 100 patients (200 paired assessments).

### Evaluation of the DART^3^ intervention

#### Outcome measures and data collection

Table 1 summarises DART^3^ outcome measures and data collection methods categorised by the RE-AIM framework. To measure outcomes, we will collect cluster and hospital level data [42], conduct surveys of healthcare providers and investigators, collect field notes and conduct research nurse check-in surveys.

**Table 1 Tab1:** DART^3^ outcomes. Outcomes, definitions, and data collection organised by RE-AIM domains

Outcomes	Information	Data source
Patient and service level outcomes		
***Primary***		
First attempt insertion success in patients identified as DIVA	One needle puncture, by one inserter, to achieve successful insertion of a functional (can be aspirated/flushed) PIVC ^2^	Hospital-based assessments
***Secondary***		
First attempt insertion success for all patients (regardless of DIVA status)	One needle puncture, by one inserter, to achieve successful of a functional (can be aspirated/flushed) PIVC ^2^	Hospital-based assessments
Number of attempts	Number of skin punctures to attempt PIVC insertion ^3^	Hospital-based assessments
Procedure outcome:	Successful PIVC insertion; time from PIVC referral to PIVC insertion (censored at 48 h); alternate device; alternate route (e.g., oral) ^4^	Hospital-based assessments
PIVC failure	Composite measure of local infection, primary bloodstream infection (BSI), occlusion, infiltration/extravasation, dislodgement (includes leaking), thrombosis and/or phlebitis ^6 7^	Hospital-based assessments
Insertion/post-insertion complications	Bruising, haematoma, nerve injury, arterial puncture, or skin injury as well as the individual components of PIVC failure (above) ^6 8^	Hospital-based assessments
PIVC dwell time	Time from PIVC insertion to PIVC removal (in hours) ^6^	Hospital-based assessments
PIVC necessity	PIVC used for fluids or medications within 24 h (excluding patients who require a prophylactic PIVC in situ as part of their treatment e.g., status epilepticus) ^5^	Hospital-based assessments
Incidence of blood stream infection	Cluster level routinely-collected rates of primary BSI and S. Aureus BSI ^9^	Hospital-based assessments
Economic outcomes		
Cost-effectiveness	Direct and indirect healthcare costs to the health system, patients/carers: (time to insertion/therapy, cost of products, number of staff, staff time, costs of responding to failed insertion including cancelled appointments)	Hospital-based assessments
Implementation outcome- reach		
Number of healthcare professionals attending Ultrasound training	Counts of clinicians attending ultrasound training	Hospital-based assessments
Number of staff accredited in ultrasound insertion	Per local ultrasound accreditation requirements	Hospital-based assessments
Implementation outcome—adoption		
Healthcare provider engagement	Proportion of patients assessed using the DIVA vein assessment tool	Hospital-based assessments
Ultrasound adoption	proportion of DIVA patients with ultrasound used at the first, or any attempt	Hospital-based assessments
Patient/carer/parent satisfaction and pain with insertion procedure	0–10 numeric rating scale ^6^	Hospital-based assessments
Inserter (initial and/or successful inserter) satisfaction with escalation pathway	0–10 numeric rating scale ^6^	Hospital-based assessments
Attitude of healthcare providers with DIVA tools	Degree of acceptability of the DIVA tools by clinicians	Key stakeholder interviews
Implementation outcome - implementation		
Fidelity	Degree that the DIVA tools are implemented as planned in original protocol	Key stakeholder interviews
Feasibility	Extent that the DIVA tools can be carried out in specific settings	Key stakeholder interviews
Outer context	Macro-level external factors including social, funding, and leadership	Key stakeholder interviews
Inner context	Micro-level internal factors including behaviours, feedback.	Key stakeholder interviews
Implementation outcome—maintenance		
Sustainability of the intervention and effectiveness	First time insertion success at 3- or 6-month sustainability assessments	Hospital-based assessments
Satisfactory of stakeholders	0–10 numeric rating scale ^6^	Key stakeholder interviews
Financial sustainability	Explored in the cost-effectiveness analysis and qualitatively through interviews with executive stakeholders.	Key stakeholder interviews
Institutionalisation of interventions	Concerned with sustaining social behavioural change	Key stakeholder interviews

*RE-AIM* Reach, effectiveness, adoption, implementation, maintenance

Data collection will be facilitated using a custom-built REDCap (Research Electronic Data CAPture http://project-redcap.org/ Vanderbilt, USA) database. Research nurses will directly enter de-identified study data (data variables and time points outlined in Table 2 and supplementary material 5) in the clinical areas using study tablets with the REDCap application configured for this trial.

**Table 2 Tab2:** Data collection time points for DART^3^

Activities	Pre-implementation	SWRCT - implementation						
		Step 1	Step 2	Step 3	Step 4	Step 5	Step 6	Step 7
Establish site-specific advisory groups	**√**							
Qualitative interviews and evidence synthesis	**√**							
Economic interviews for PIVC insertion procedures	**√**	**√**	**√**	**√**	**√**	**√**		
Co-develop DIVA tool and escalation pathway	**√**							
Pilot-test and evaluate DIVA tool and escalation pathway prototypes for reliability, acceptability and reproducibility	**√**	**√**						
Implementation of site-specific DIVA tools across the 3 hospitals, 12 clusters in a staggered manner			**√**	**√**	**√**	**√**		
Cluster 1 from each hospital			**√**	**√**	**√**	**√**		
Cluster 2 from each hospital				**√**	**√**	**√**		
Cluster 3 from each hospital					**√**	**√**		
Cluster 4 from each hospital						**√**		
Patient and service level outcomes (REDCap CRF)		**√**	**√**	**√**	**√**	**√**	**√**	**√**
DIVA PIVC time-in-motion data for cost-effectiveness analysis		**√**	**√**	**√**	**√**	**√**		
Implementation data collection (questionnaires, field notes)		**√**	**√**	**√**	**√**	**√**		
Sustainability activities							**√**	**√**
Organisational guideline incorporation							**√**	**√**
Process evaluation interview						**√**	**√**	**√**

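### As worded, the PIVC necessity rule (H10) scores a catheter that fails before its first use as unnecessary, even when IV therapy was needed

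*Protocol article*

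**What the plan says.** In the protocol article, Table 1 (secondary outcomes, PIVC necessity row) defines the outcome as "PIVC used for fluids or medications within 24 h". It names one exception: "excluding patients who require a prophylactic PIVC in situ as part of their treatment e.g., status epilepticus". The row gives neither the start of the 24 h clock nor the denominator.

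The matching hypothesis, H10, is that the pathways' implementation "Reduces rates of unnecessary PIVCs". The article does not define an unnecessary PIVC separately, so the natural reading is the complement of the necessity row.

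H7 is that the same implementation "Reduces post-insertion PIVC failure and complications". The failure composite in Table 1 covers local infection and primary bloodstream infection together with "occlusion, infiltration/extravasation, dislodgement (includes leaking), thrombosis and/or phlebitis". It sets no condition that the PIVC was used before it failed.

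**The concern.** H10 is about avoidable insertion, but the rule measures use. A PIVC can go unused for two different reasons: nobody needed it, or it failed before anyone could use it. The rule as worded puts both in the same class. The prophylactic exception shows that a catheter can be needed yet unused, but the row makes room for only one such case.

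The misclassification need not be equal in the two phases. H7 predicts fewer failures after implementation. The Background section suggests a mechanism: landmark insertion cannot confirm that the tip lies in the vessel rather than the tissue, and usual care is described under Randomisation and blinding as predominantly landmark. Any bias would therefore favour the intervention. H10 could be reported as a reduction in avoidable PIVCs when what changed was catheter survival to first use. Research staff are also unblinded, so an unsettled class would be sorted by people who know the phase.

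**Working it through.** The article states no rate, sample size or power for PIVC necessity, so there is no figure to reproduce. The check has two parts.

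**1. Which PIVCs are affected.** Applying the Table 1 wording to each case:

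- Used within 24 h, then fails: necessary. No problem.
- Never used, no therapy needed: unnecessary. Correct.
- Never used, prophylactic: excluded.
- Needed, but fails before first use: not used, no exception applies, so unnecessary. It is also a failure under H7.

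Only the last group is misclassified. It is narrow. First-attempt success already requires one puncture by one inserter "to achieve successful insertion of a functional (can be aspirated/flushed) PIVC". If the same standard applies to any successful insertion, the group is limited to failures between a working insertion and the first dose.

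**2. Illustrative size.** Let u be the share of PIVCs that are truly avoidable, held equal in both phases. Let f be the probability that a needed PIVC fails before first use. Then

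apparent unnecessary rate = u + (1 − u) × f

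and the share of that rate due to failure is (1 − u) × f divided by it. Both u and f, and the halving of f after implementation, are assumptions; H7 gives a direction only.

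| u | f, control → implementation | Apparent rate, control | Apparent rate, implementation | Spurious gain (points) | Failures as share of control rate |
|---|---|---|---|---|---|
| 20% | 1% → 0.5% | 20 + 80 × 0.01 = 20.8% | 20 + 80 × 0.005 = 20.4% | 0.4 | 4% |
| 10% | 2% → 1% | 10 + 90 × 0.02 = 11.8% | 10 + 90 × 0.01 = 10.9% | 0.9 | 15% |
| 10% | 5% → 2.5% | 10 + 90 × 0.05 = 14.5% | 10 + 90 × 0.025 = 12.25% | 2.25 | 31% |
| 10% | 6% → 3% | 10 + 90 × 0.06 = 15.4% | 10 + 90 × 0.03 = 12.7% | 2.7 | 35% |
| 5% | 10% → 5% | 5 + 95 × 0.10 = 14.5% | 5 + 95 × 0.05 = 9.75% | 4.75 | 66% |

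As a rough guide to whether such a gap would be noticed: the Sample size section implies 8 + 12 = 20 patients per cluster per period. With the Table 2 roll-out over 12 clusters and five periods, control cells number 12 + 9 + 6 + 3 + 0 = 30 and implementation cells also 30, so 30 × 20 = 600 observations per phase. A plain comparison of two proportions (two-sided 0.05, clustering and period effects ignored) reaches significance with probability about 4% in the first row, 7% in the second, 21% in the third and 71% in the last. The first two are close to what chance alone would give.

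**The case against.** The article does not say in terms how a PIVC that fails before first use is scored. The necessity row carries footnote marker 5, whose text is not shown, and the analysis plan (Supplementary material 3) and data variables (Supplementary material 5) are not shown either. Any of these could exclude such PIVCs or sort them by reason for removal. A reader might infer that the trial does count early failures as unnecessary and that H10 is in part a measure of failure. The documents support only the conditional statement: that is what the visible wording does if nothing else qualifies it. The objection still does not dispose of the point, because the row states a rule and an exception, and applied as written that rule misclassifies a definable group.

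A reader might also infer that counting one event under both H7 and H10 is an error in itself. It is not. They are separate secondary hypotheses that are never summed, and the article overlaps outcomes openly, for example by listing the components of failure again under complications. The difficulty is what H10 would be taken to mean, not the overlap.

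The last strong reading is that H10 would be falsely declared met. That is not shown. The affected group is narrow, no document gives its size, and at low values of f the effect is negligible.

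Finally, a use-based 24 h measure is simple and objective. That is a fair reason to keep it as the base rule and to separate out only the failed catheters.

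**Conclusion.** The point holds in limited form. On the visible wording of Table 1, a needed PIVC that fails before first use is scored unnecessary, and if H7 is true this moves H10 in the favourable direction without fewer avoidable insertions. The direction follows from the text; the size does not. With avoidable insertion held constant and early failure assumed to halve, the spurious gain is about 0.4 to 3 points when 1% to 6% of needed PIVCs fail before first use. It approaches 5 points only if as many as 10% do. All of these rates are assumptions.

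The conclusion also assumes that the unseen footnote and supplementary materials do not already deal with these PIVCs. It concerns one secondary outcome. The primary outcome, the sample size and the primary model are untouched, so this is a minor but worthwhile clarification.

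**What to change.** Keep use within 24 h as the base rule and the prophylactic exception as it stands, and add a third class:

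- **Used** within 24 h.
- **Unused because failed**: failed before first use, and either IV therapy was given within 24 h through a replacement vascular device or it was still prescribed when the PIVC failed.
- **Unused for other reasons**: the only class scored as unnecessary.

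Base H10 on the third class and report the second separately by phase. The prescription limb is needed because a rule resting only on a replacement device would still misclassify patients whose re-access takes more than 24 h or who are switched to an oral route, and H5 and H6 expect both time to therapy and alternate route use to change with phase.

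Keep the failed PIVCs in the denominator. Dropping them leaves a small residual bias: with u = 10% and f falling from 6% to 3%, the rates would be 10 / (100 − 5.4) = 10.6% and 10 / (100 − 2.7) = 10.3%, instead of 10% in both phases.

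The cost is a change of outcome wording, one extra REDCap field, and slightly more chart reading for PIVCs that fail in the first 24 h. Failure, dwell time and alternate device use are already collected, and follow-up already runs to 48 h after removal. If the footnote or the supplementary materials already contain such a rule, carrying it into the Table 1 row is enough.
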